# The effects of Phoniatric PREhabilitation in Head and Neck Cancer patients on Aspiration and Preservation of Swallowing (PREHAPS): study protocol of a monocentric prospective randomized interventional outcome-blinded trial

**DOI:** 10.1186/s13063-024-08010-2

**Published:** 2024-03-22

**Keywords:** Prehabilitation, Head and neck cancer, Swallowing, Dysphagia, Aspiration, FEES, Phoniatrics, Quality of life, Randomized controlled trial

## Abstract

**Background:**

Dysphagia, with its negative impact on life expectancy and quality of life, is a major side effect of head and neck squamous cell carcinoma (HNSCC). In a typical Head and Neck Cancer Center, more than half of patients are affected. Improving treatment, and ideally prevention respectively prehabilitation, therefore seems more than desirable.

**Methods:**

The study is planned as a monocentric, prospective, outcome-blinded, randomized interventional study comparing an advanced phoniatric-logopedic prehabilitation with a control (standard of care). Seventy patients (30 control group, 30 intervention group, 10 drop-out rate of 15%) with an initial diagnosis of invasive HNSCC and curative treatment intention will be included over a period of 17 months. In addition to the previous standard, both groups will undergo both detailed subjective assessment of swallowing function and quality of life by means of various questionnaires and objective analyses by bioelectrical impedance measurements and phoniatric endoscopic swallowing examinations. In the intervention group, risk-related nutritional counseling (face-to-face) and phoniatric-logopedic prehabilitation are provided: detailed counseling with video demonstration and exercises to strengthen and improve the range of motion of the oral, pharyngeal, and laryngeal muscles (guided by exercise diary). Controls are performed at 6 weeks, 3 and 6 months, and 9 or 12 months after the end of therapy during the regular tumor follow-up. Primary study endpoints are swallowing function and emotional distress at 6 weeks of control visit.

**Discussion:**

Prehabilitation measures have already proven successful in other patient groups, e.g., transplant patients. In the field of head and neck oncology, interest in such concepts has increased significantly in recent years. However, usually, only subgroups, e.g., patients with swallowing problems after radiochemotherapy alone, are in focus. Our study aims to investigate the general benefit of prehabilitation with regard to swallowing function, which is so important for protection of aspiration and quality of life.

**Trial registration:**

German Clinical Trials Register DRKS00029676. International Clinical Trials Registry Platform DRKS00029676. Registered on 19 July 2022.

**Supplementary Information:**

The online version contains supplementary material available at 10.1186/s13063-024-08010-2.

## Background

Head and neck squamous cell carcinoma (HNSCC) is the sixth most common malignant tumor disease, mostly affecting the upper aerodigestive tract [1]. At a typical Head and Neck Cancer Center, approximately 55% of patients currently suffer from dysphagia [2]. In subgroups with, e.g., oropharyngeal carcinomas, such disorders occur in up to 80% of cases, fatal because in this group the proportion of younger patients is increasing worldwide due to the association with HPV (human papillomavirus) and already reaches 30–40% in Germany [3]. Especially these younger patients rightly expect special attention to swallowing disorders because of disease and therapy. Last, but not least, clinically relevant anxiety or depression symptoms are regularly associated with dysphagia, in almost 50% of cases [4], hardly surprising considering the central social importance of eating and drinking together. Elderly patients (over 65 years of age) are at mortality risk from dysphagia, especially from aspiration pneumonia [5]. Often, patients with HNSCC have low socioeconomic status and relevant comorbidities that lead to retirement in up to 50% of cases after therapy [6]. In contrast, early rehabilitation of dysphagia appears to mitigate the financial consequences of the disease [7]. Swallowing disorders in head and neck tumor patients are thus highly relevant for effective therapeutic interventions not only because of the directly associated limitations of quality-of-life (QoL), but also because of the risk of complications.

In Germany, the focus is on post-therapeutic rehabilitation, and the treatment of preexisting swallowing disorders disregards preventive efficacy, both before and after oncological therapy. The introduction and implementation of a complex pre-therapeutic phoniatric intervention (diagnostics by means of endoscopic examination of swallowing function as well as comprehensive questionnaires and patient self-reports; therapy by means of individual logopedic counseling with instructions for exercise treatment of swallowing function) as well as a comprehensive malnutrition screening with nutritional counseling will therefore be tested in a study in the setting of a University Head and Neck Cancer Center in Germany. The benefit of such a measure prior to treatment of a representative cohort of HNSCC patients is currently unknown, as is any harm. In the context of post-therapeutic rehabilitation, logopedic swallowing therapy is of great importance, whereas a harmful effect has not been demonstrated here either.

We expect that this approach will improve swallowing function and also reduce the emotional burden of patients, so that not only the oncological outcome, but also the peri- and post-therapeutic QoL can be significantly improved.

## Methods

### Study design

The study is designed as a monocentric, prospective, randomized (parallel group; allocation ratio 1:1), outcome-blinded, controlled interventional trial (exploratory RCT) at the Head and Neck Cancer Center of the University Hospital Regensburg. The intervention consists of individual information and risk consulting, individual logopedic counseling with instructions for exercise treatment of swallowing function, and risk-related nutritional counseling (face-to-face). In the control group, patients are treated according to the currently applicable standard of care described in the guidelines on laryngeal cancer [8] and oral cavity cancer [9] as well as in the survey on Head and Neck Cancer Centers of the German Cancer Society (https://www.krebsgesellschaft.de/zertdokumente.html).

### Outcomes

All patients participating in the study are analyzed by means of various questionnaires in addition to the therapy standard of the Head and Neck Cancer Center Regensburg:EORTC-QLQ-C30 for the general assessment of QoL [10]EORTC-QLQ-HN43 to assess the QoL of patients with HNSCC [11]Dysphagia Handicap Index (DHI) for measuring the handicapping effect of dysphagia on the physical, functional, and emotional aspects of people’s lives [12]Hospital Anxiety and Depression Scale (HADS) for assessing anxiety and depression [13]Functional Oral Intake Scale (FOIS-G) to analyze oral food intake [14]

In addition, a bioelectrical impedance analysis, a determination of the body mass index (BMI), and measurement of serum albumin level take place.

Furthermore, a detailed phoniatric diagnosis of swallowing (Functional Endoscopic Evaluation of Swallowing (FEES)) regarding restrictions of oral nutrition and aspiration risk, which is objectively evaluated by means of the Penetration-Aspiration Scale (PAS) [15] and the Yale Residue Scale (YRS) [16], is performed.

Primary study endpoints, 6 weeks after the end of therapy:Swallowing function (objectively assessed using FEES: PAS, YRS, subjectively using DHI and FOIS-G)Emotional distress: anxiety and depression (HADS)

Secondary study endpoints 6 weeks, 3 and 6 months, and 9 or 12 months after the end of oncologic therapy:Swallow-related QoL (DHI; EORTC-QLQ-HN43; FOIS-G).◦ Time to decannulation◦ Percentage of nutrition by gastric feeding tube/time of dependence on enteral nutritional substitution via a gastric feeding tube◦ Incidence of complications (aspiration pneumonia)Inpatient length of stay, incl. readmissionNutritional status (BMI, albumin, bioelectrical impedance analysis)General QoL (EORTC-QLQ-C30)Occupational reintegrationSubgroup analyses regarding older patients (> 65 years) and patients with weaker social status

#### Eligibility criteria of study participants

Inclusion criteria:Initial diagnosis of invasive HNSCC

Exclusion criteria:T1 glottic carcinoma, salivary gland tumors, sinus, nasal cavity carcinomas, lip carcinomas, skin carcinomasPlanned laryngectomy, total glossectomy, esophageal dysphagiaNo curative therapyState after therapy of carcinoma of the upper aerodigestive tract or esophageal carcinomaState after radiotherapy in the head and neck regionHigher-grade cognitive impairment (e.g., dementia, Korsakow syndrome)Psychomotor impairment (e.g., Parkinson's disease), previous neurological diseases with dysphagia (e.g., post apoplexy)Age < 18 yearsECOG > 2Patient is unable to complete questionnaires even with assistance (inadequate ability to read and write, higher grade inadequate hearing loss).Language barrierPregnancy/breastfeeding

### Interventions

For a detailed analysis of the effects of Phoniatric PREhabilitation in Head and Neck Cancer patients on Aspiration and Preservation of Swallowing, two study arms were designed (Table 1). In the intervention group, additional measures take place compared to the control group:General information and risk counseling on the swallowing examination, also for the prevention of dysphagia before and during therapy with video demonstration [17], if necessary, also to accompanying relatives.Logopedic exercises to strengthen and improve the sensitivity and range of motion of oral, pharyngeal, and laryngeal muscles (tongue, larynx, jaw, e.g., Mendelsohn maneuver, Shaker maneuver, effortful swallow, supraglottic swallowing technique). The exact therapeutic procedure is based on an individual protocol. The patient is instructed to discontinue or modify in-home exercises (eating rules, individual exercise protocol with recommended dosage, documentation in exercise diary). The prescribed dose of exercise treatment takes into account not only the need but also the expected patient’s adherence to therapy. It includes at least 10 repetitions 3 times a day for each of, e.g., 5 forms of exercises [4], so that a total dose of 150 exercises per day is achieved. Even in the case of minor symptoms, preventive counseling and exercise treatment are carried out with a view to the future. After 3–7 days, a speech therapist conducts a control interview (face-to-face or by telephone) based on the exercise diary. If it seems necessary, an intervention can take place at short notice.Additional nutritional risk screening [18] and risk-related nutritional counseling (face-to-face), performed by staff of the Department of Internal Medicine III, Hematology and Oncology.

**Table 1 Tab1:** Study design—intervention versus control group

Measures’ description	Study arms	
	**Intervention**	**Control**
**Pre-therapeutic standard**		
Standardized non-phoniatric, medical assessment of swallowing function, if necessary phoniatric-logopedic diagnostics and therapy according to standard; in some cases low-frequency therapy already before/during therapy, usually by cost adaptation	X	X
Tumor board	X	X
Medical information (diagnosis, surgery or radiotherapy)	X	X
Psycho-oncological screening (Hornheider questionnaire), intervention if necessary	X	X
Contact and advise social service	X	X
PEG, if necessary	X	X
Nutritional Risk Screening (NRS)—prescreening in nursing history	X	X
Proactive information about smoking cessation (flyer)	X	X
**Baseline values (both groups, in addition to the previous standard)**		
EORTC-QLQ-C30 [10], EORTC-QLQ-HN43 [11], Dysphagia-Handicap-Index (DHI) [12], Hospital Anxiety and Depression Scale (HADS) [13]	X	X
NRS main screening, risk-related nutritional counseling (face-to-face); bioelectrical impedance analysis	X	X
Phoniatric diagnostics (FEES) regarding oral feeding restrictions and aspiration risk: Penetration Aspiration Scale (PAS) [15]; Functional Oral Intake Scale (FOIS-G) [14]; Yale Residual Scale [16]	X	X
**Intervention**		
Phoniatric-logopedic PREhabilitation General information and counseling, also for prevention of dysphagia before/during therapy, video demonstration [17], if necessary also by accompanying relatives, exercises to strengthen and improve the range of motion of oral, pharyngeal, and laryngeal muscles (tongue, larynx, jaw, e.g., Mendelsohn, Shaker maneuvers, “effortful swallow,” supraglottic swallowing technique) and sensitivity. Therapeutic approach according to individual protocol. Instructions for home exercise (eating rules, individual exercise protocol with recommended dosage, instructions for exercise diary)	X	-
Follow-up interview, based on exercise diary, after max. 1 week, by phoniatrics, speech therapy and nutrition counseling, face-to-face or by telephone	X	-
**Oncological therapy**		
**Postinterventional outcome measures at 6 weeks and 3, 6, and 12 months after the end of oncologic therapy**		
Questionnaires: EORTC-QLQ-C30 [10]), EORTC-QLQ-HN43 [11]), FACE-Q Head and Neck Cancer [19]), Dysphagia-Handicap-Index (DHI) [12]), Hospital Anxiety and Depression Scale (HADS) [13])	X	X
Phoniatric-logopedic follow-up (FEES) regarding oral feeding restrictions and aspiration risk, Penetration Aspiration Scale (PAS) [12]; Functional Oral Intake Scale (FOIS-G) [14]; Yale Residual Scale [13] and on the progress of therapy (exercise diary)	X	X
**Follow-up treatment (AHB) after 6 weeks, according to patient preference**		

### Sample size and recruitment

Since this type of therapeutic approach was not studied yet in this form, it was not possible to estimate an expected effect size for a sample size calculation. Therefore, the study design for the present project was chosen with a complex family of endpoints to obtain first estimates of treatment effects for the clinically relevant endpoints with the consequence that no sample size calculation based on an expected treatment effect of one primary endpoint was performed. Instead, sample size considerations are based on assumptions about possible effect sizes of different endpoints (primary endpoint family) with the aim to get reliable and valid effect estimates for a following more extensive multicenter clinical trial. After sharpening the focus, the results of this study will be used to initiate a multicenter confirmation study, e.g., within the framework of the BZKF (Bavarian Center for Cancer Research, Head and Neck Tumor Study Group). According to the publication by Guillen-Sola [20] we assume median effect sizes within the primary endpoint family. They state an effect in the Penetration-Aspiration-Scale of 2 Units and a difference ≥ 10 units in the tests of quality of life (EORTC-QLQ-C30 and EORTC-QLQ-HN35). This is also the expectation of the therapy based on our clinical experience. Here, a “median effect size” methodologically means a Cohen’s *d* of approximately 0.5 or half a standard deviation [21]. 

To obtain sufficient accuracy for the estimation of treatment effects due to the performed intervention as well as for the planning of a confirmative follow-study, *n* = 30 patients per study arm (*n* = 60 in total) are to be analyzed under the assumption of median effect sizes regarding the endpoints of the primary endpoint family [22]. Assuming a drop-out rate of 15%, *n* = 70 patients have to be included and randomized in the study. In the recruitment period of 17 months, we assume a potential study population of 350 patients (250 primary cases in the Head and Neck Cancer Center per year). Considering the increase in higher tumor stages due to the corona pandemic, we expect 40% of patients (*n* = 140) to meet all inclusion and exclusion criteria, of which 50% of patients (*n* = 70) are likely to give informed consent. Thus, inclusion of 70 patients in the planned recruitment period is realistic. Screening and identification of potential study patients will occur during the patient’s first inpatient stay (primary diagnosis, histology acquisition, pan-endoscopy, staging). After the tumor diagnosis has been confirmed, the first contact with the potential study patient is made in the Ear, Nose and Throat Clinic and the Clinic for Oral and Maxillofacial Surgery (usually after the interdisciplinary tumor board) by physicians from the clinics with the support of the study assistance. The detailed study information as well as the study inclusion is carried out by the medical staff of the Section of Phoniatrics and Pediatric Audiology. 

The study is explained in detail to the patient by a physician from the Section of Phoniatrics and Pediatric Audiology. Subsequently, the patient gives an informed consent to participate in the study by means of a written declaration of consent. As part of the consent process, the participant will be asked whether the data collected may also be used for questions unrelated to the study but related to the study purpose. The participant can agree to such use or refrain from doing so. Randomization is performed prior to the intervention, after informed and signed consent, via REDCap database. Each randomization is documented and signed by the investigator.

### Statistical analysis

The primary outcome measure is a complex family of endpoints including swallowing function (subjectively using DHI, FOIS-G, and objectively using FEES) and anxiety and depression (HADS) 6 weeks after the end of therapy. Each questionnaire score will be calculated using the associated manual. The two study groups will be compared for each endpoint using analysis of covariance (ANCOVA). The respective endpoint at the time point after 6 weeks is included in the model as the dependent variable, the study group as factor, and the respective baseline value at baseline as covariate. To check the endpoints, the intention-to-treat collective will be used as the evaluation collective. Analyses will also be evaluated on the per-protocol collective as a control. Established, clinically relevant effect sizes will be used as a comparison to evaluate the effects (estimated marginal means and 95% confidence intervals) and their benefit to patients. A panel of experts (phoniatrics, ENT, maxillofacial surgery, speech therapy, study assistance, biometry) will evaluate which changes in primary outcome parameters should be interpreted as clinically relevant. In addition, subgroup analyses will be performed regarding older patients (> 65 years) and patients with weaker social status. The concept of complex pre-therapeutic phoniatric prehabilitation is considered promising if there is a consistent advantage over the control group within the complex family of outcomes.

Secondary study endpoints 6 weeks, 3 and 6 months, and 9 and/or 12 months after the end of oncologic therapy will be considered exploratively: swallowing-related QoL, subjectively perceived swallowing function, incidence of aspiration pneumonia, general QoL, nutritional status, time to decannulation, nutritional percentage by gastric feeding tube, time of dependence on enteral nutritional substitution via gastric feeding tube, duration of inpatient stays, and occupational reintegration.

The analysis of secondary endpoints is purely descriptive and exploratory. Depending on the type of endpoint, covariance analyses for metric endpoints, logistic regressions for dichotomous endpoints, or simple tests such as Student’s *t*-tests, Wilcoxon Mann–Whitney *U* tests, or chi-square tests are used.

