### Randomization and blinding

#### Randomization

Randomization of a patient is stratified according to UICC stage (8th edition) into stratum I (UICC I and II) and stratum II (UICC III and IV). This considers that patients treated by surgery alone are generally assigned to the earlier tumor stages UICC I and II and are less likely to require adjuvant therapy. Patients with an indication for adjuvant radiotherapy or radiochemotherapy or primary radiotherapy or simultaneous radiochemotherapy are more likely to belong to the advanced tumor stages UICC III and IV. Randomization will be computerized (REDCap database) by a physician from the Section of Phoniatrics and Pediatric Audiology prior to intervention, after informed and signed consent (see above).

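### Randomisation is stratified by UICC stage but the primary ANCOVA leaves the stratum out; adding it costs one degree of freedom and would narrow the intervals if stage predicts outcome beyond baseline

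*Protocol article*

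**What the plan says.** The Study design section describes a two-arm trial ("parallel group; allocation ratio 1:1"). Under Randomization, "Randomization of a patient is stratified according to UICC stage (8th edition"), with stages I and II in one stratum and III and IV in the other. The reason given is treatment modality: "patients treated by surgery alone are generally assigned to the earlier tumor stages UICC I and II and are less likely to require adjuvant therapy", whereas those with an indication for radiotherapy or radiochemotherapy "are more likely to belong to the advanced tumor stages UICC III and IV".

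The Statistical analysis section compares the arms on each primary endpoint by ANCOVA and lists the terms: the 6-week value as dependent variable, "the study group as factor, and the respective baseline value at baseline as covariate". UICC stage is not among them, and no other section brings it in. Results are to be reported as estimated marginal means with 95% confidence intervals.

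**The concern.** Stratified allocation balances stage between the arms, so stage contributes little to the random variation of the treatment contrast. A model without stage still counts stage differences as residual error. If stage is prognostic after baseline adjustment, the reported standard error then exceeds the real sampling variability of the estimate, and intervals and tests are conservative.

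The protocol's rationale makes such a contribution plausible for swallowing. Stage stands in for treatment given after baseline and before the 6-week visit, which a pre-treatment DHI, FOIS-G, PAS or YRS score cannot reflect. The rationale says nothing about anxiety or depression, so for HADS the case is weaker.

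Interval width matters in this trial. The Sample size and recruitment section sets no power target; it justifies 30 patients per arm by the accuracy of the effect estimates and by their use in planning a multicentre trial.

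**Working it through.** **Inputs from the protocol.** Two strata; 1:1 allocation; 70 randomised and 60 analysed (30 per arm); drop-out 15%; assumed effect d about 0.5; 95% intervals, taken here as two-sided 5%. No alpha, sidedness or power is stated.

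**The plan's own figure.** 60/(1 − 0.15) = 70.6, so 71; 60 × 1.15 = 69. The stated 70 lies between them and is reproduced. There is no stated power to reproduce.

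**Assumptions not in the documents.** R², the share of the variance left after baseline adjustment that stage explains, is varied from 0 to 0.30. Baseline–outcome correlation 0.5; 65% of patients in the III/IV stratum; permuted blocks of 4; normal outcomes; drop-out at random.

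**Formulas.**
- Interval width as written, relative to the model with the stratum: 1/√(1 − R²). For R² = 0.05, 0.10, 0.20, 0.30 this gives 1.026, 1.054, 1.118, 1.195.
- True error of the nominal 5% test under perfect balance: 2 × [1 − Φ(1.96/√(1 − R²))] = 4.4%, 3.9%, 2.8%, 1.9%.
- Half-width as written with correlation 0.5: residual SD √(1 − 0.25) = 0.866; t(57) = 2.002; 2.002 × 0.866 × √(2/30) = 0.448 SD. Power at d = 0.5 from the noncentral t is 59.4%.

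**Simulation.** 8,000 trials per scenario, 70 randomised within strata, 60 analysed. Each cell gives the model as written, then the model with the stratum. Half-widths are in SD units; half-width and error are under no effect, power at d = 0.5.

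| R² | Half-width | Error | Power |
|---|---|---|---|
| 0 | 0.450 / 0.451 | 5.4% / 5.3% | 59.0% / 59.0% |
| 0.05 | 0.450 / 0.439 | 4.5% / 4.9% | 59.5% / 61.9% |
| 0.10 | 0.451 / 0.428 | 4.0% / 4.7% | 60.1% / 64.1% |
| 0.20 | 0.451 / 0.404 | 3.0% / 4.9% | 58.3% / 67.3% |
| 0.30 | 0.451 / 0.377 | 2.3% / 5.2% | 59.7% / 73.5% |

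Monte Carlo standard errors are about √(0.05 × 0.95/8000) = 0.24 points for error and √(0.6 × 0.4/8000) = 0.55 points for power. The width ratios (for example 0.451/0.404 = 1.12) match the formula. The simulated errors lie slightly above the formula values, which assume perfect balance; unfilled blocks and drop-out disturb it a little.

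**Bias or reported precision?** The mean estimate was 0.500 to 0.505 at a true 0.5 under both models. At R² = 0.20 under no effect, the actual SD of the estimate was 0.207 as written and 0.202 with the stratum. The standard error implied by the reported interval is 0.451/2.002 = 0.225 as written and 0.404/2.003 = 0.202 with the stratum. The estimator itself is nearly as good either way; what is wrong is the interval around it.

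**The case against.** The strongest reply is that this is a small efficiency point in a trial that calls itself exploratory. At R² = 0.10 the half-width changes by 0.451 − 0.428 = 0.023 SD, and at 0.20 by 0.047 SD. The trial sets no alpha or power and judges success by a consistent advantage across the endpoint family. No document gives R², and at R² = 0 the two models are indistinguishable. All of this stands; it limits the size of the point but does not remove it.

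It could also be said that an article condenses the full protocol and that an analysis plan may add the stratum. It may, but the article lists the model terms, so this is a stated model rather than an omitted detail.

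Stronger readings that the documents do not support:
- **That the result is biased or the test too liberal.** The estimate is unbiased and any error is on the conservative side.
- **That the loss is certain because the protocol calls stage strongly prognostic.** It does not. It links stage to treatment modality in hedged terms and makes no statement about stage and PAS, YRS, DHI, FOIS-G or HADS.
- **That power starts at 49%.** That is the two-sample figure for 30 per arm at d = 0.5. The planned model already adjusts for baseline, so it is not the figure for this analysis unless baseline explains nothing or d is read in residual SDs.
- **That every secondary analysis needs the stratum.** The t, Mann–Whitney and chi-square tests have no place for a covariate. In logistic regression, adding a prognostic factor changes the odds ratio being estimated and does not shrink its standard error on the log scale, so the interval-width argument does not carry over.

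**Conclusion.** The point holds as a conditional, essentially free improvement. The model as written omits the randomisation stratum. If stage explains 5–20% of the variance remaining after baseline adjustment, the 95% intervals are about 3–12% too wide and the true error of a nominal 5% test is about 4.5–3.0%; at 30% the figures are 20% and 2.3%. With a baseline–outcome correlation of 0.5, including the stratum raises simulated power at d = 0.5 from about 59% to 62–67% over the 5–20% range.

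The direction is secure once stage is prognostic beyond baseline. The size rests on R² and, for power, on the correlation, neither of which the documents give. R² may also differ between endpoints, and the protocol offers least support for a gain on HADS.

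**What to change.** Name the UICC stratum (I/II against III/IV) as a fixed factor, alongside study group and baseline value, in each primary ANCOVA and in the covariance analyses of metric secondary endpoints, before any data are analysed by arm.

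The cost is one line of text and one degree of freedom (57 to 56 with 60 patients analysed). If stage turns out to explain nothing, the simulated half-width moves from 0.450 to 0.451 SD. The simple secondary tests and the logistic regressions can stay as they are. A sensitivity analysis that also adjusts for the treatment modality planned before randomisation is optional.
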